## 1. Background

Radiotherapy (RT) serves as a principal therapeutic modality for malignant head and neck tumors. Cumulative evidence indicates that unplanned radiotherapy interruption is a robust independent predictor of poorer survival outcomes across various cancers. This association is particularly more pronounced in patients with head and neck malignancies, where studies indicate that each day of interruption reduces tumor control by at least 1%. Notably, between 41.6% and 63.6% of patients with head and neck cancer experience such interruptions, primarily due to compromised nutritional status and psychological distress. Research indicates that 37.9% of cancer patients receiving radiotherapy experience weight loss during treatment. A study based on the Patient-Generated Subjective Global Assessment (PG-SGA) scale revealed that the incidence of malnutrition in patients with malignant head and neck tumors rose significantly from 24% before radiotherapy to 88% afterward. Moreover, 71.5% of patients with malignant head and neck tumors experience varying degrees of anxiety, depression, and other psychological disorders. This establishes a detrimental cycle between nutrition and psychological well-being, which may interrupt radiotherapy and impact patients' quality of life (QoL).

In China, patients often receive their RT in an outpatient setting, and nutrition clinics and psychological clinics are available only in some larger-scale hospitals, which restricts patients' access to nutritional and psychological support. Simultaneously, both oncologists and a majority of cancer patients often underestimate the importance of nutritional and psychological care, resulting in delayed interventions. These circumstances can lead to the interruption of RT, with reported rates ranging from 23.5% to 42.5% for head and neck tumors. Radiotherapy interruption directly undermines tumor control efficacy, thereby jeopardizing long-term survival outcomes in patients.

Therefore, the SHINE-MDT (comprising oncology nurse specialists, radiation oncologists, medical oncologists, dietitians, psychotherapists, and rehabilitation physicians) was established to provide nutritional, psychological, and rehabilitated support for patients with

malignant head and neck tumors throughout the entire RT period. To assess the effect of SHINE-MDT on patient outcomes, we conducted a randomized clinical trial. We hypothesized that this SHINE-MDT approach would reduce radiotherapy interruption rates and improve patients' QoL compared to usual care.

## 2. Objectives of the research

- **Primary Objectives:** To investigate the effect of SHINE-MDT on the rate of radiotherapy interruption.
- **Secondary objective:** To evaluate patients' QoL, nutritional status, psychological well-being, rehospitalization rate, and tumor response.
  - To investigate the impact of SHINE-MDT on patients' QoL based on the European Organization for Research and Treatment of Cancer (EORTC) Quality-of-life Questionnaire Core 30 (EORTC QLQ-C30) and Head and Neck Cancer Module (EORTC QLQ-H&N35).
  - To investigate the effect of SHINE-MDT on patients' nutritional status based on the Nutritional Risk Screening 2002 (NRS 2002) and PG-SGA.
  - To investigate the impact of SHINE-MDT care on patients' psychological status based on the Distress Thermometer (DT), Patient Health Questionnaire-9 (PHQ-9), and Hospital Anxiety and Depression Scale (HADS)
  - To investigate the impact of SHINE-MDT on the rehospitalization rate.
  - To investigate the effect of SHINE-MDT on tumor response according to RECIST version 1.1.

## 3. Study design, methods and procedures

### 3.1 Study design

A two-arm, randomized, single-center, prospective study.

### 3.2 Methods and Procedures

#### ➤ **Patients Enrollment:**

- Inclusion criteria:

1. Male or female patients:  $\geq 18$  years;
2. Expected survival  $\geq 6$  months;
3. Pathologically confirmed malignant head and neck tumors (including nasopharyngeal carcinoma) without distant metastasis;
4. Scheduled to undergo definitive radiotherapy or postoperative adjuvant radiotherapy;
5. Systemic functional status Eastern Cooperative Oncology Group (ECOG) (Appendix 2) rating  $\leq 2$ ;
6. Adequate cognitive and reading abilities to complete the questionnaire;
7. Sign the informed consent.

- Exclusion criteria:

1. Other malignant tumors aside from head and neck malignancies (excluding treated basal cell carcinoma of the skin or in situ cervical cancer);
2. History of prior head and neck radiotherapy;
3. History of mental disorders diagnosed by a psychiatrist according to ICD-10 criteria, or history of psychotropic medication use;
4. Absolute contraindications for head and neck radiotherapy;
5. Uncontrolled systemic diseases that significantly impact the quality of life, such as poorly controlled diabetes, heart failure (NYHA classification III-IV; Appendix 4), or interstitial lung disease;

- Withdrawal Criteria:

Withdrawal criteria include, but are not limited to:

1. Patients who cancel their informed consent;
2. Patients who are non-compliant with the study protocol;

3. Patients assessed by researchers as unsuitable to continue.

➤ **Randomization and Blinding**

All patients were randomly assigned in a 1:1 ratio to one of two groups: the UC group or the SHINE-MDT group. The randomization process was done using a computer-generated random assignment list based on a randomized permutation block design.

Group allocation was performed using block randomization, with eligible patients being randomly assigned in a 1:1 ratio to either the UC group or the SHINE-MDT group. The statisticians designed the block size, assignment order list, and random numbers, with an equal number of patients in the UC and SHINE-MDT groups within each block. Only the statistical design personnel knew the block size (variable block size of 4 or 6). Concealment was achieved using opaque, sealed envelopes. The statistical design personnel prepared sealed envelopes with random group assignments for each participant. Sequentially, the envelopes were opened upon participant enrollment, determining the group assignment according to the allocation disclosed within the envelope.

➤ **Intervention Strategies**

● **Anti-Cancer Treatment Regimen**

All enrolled patients received radiotherapy delivered in daily fractions of 1.8 - 2.2 Gy, administered five times per week for 6 - 6.5 weeks, resulting in a total tumor dose of 60 - 72 Gy. The clinical target volume and organs at risk were delineated in accordance with consensus guidelines. Concurrent chemotherapy consisted of cisplatin 100 mg/m^2 every 3 weeks.

● **Intervention Measures for the Usual Care Group**

In the control group, based on the patients' questionnaire results, the radiation oncologist and risk-stratified nurses would provide dietary or psychological guidance or recommend appropriate outpatient clinics (nutrition, psychology, or rehabilitation) for patients to seek further consultation. Patients had the autonomy to decide whether or not

to schedule appointments at the recommended outpatient clinics. This reflects the routine medical practice commonly experienced by patients undergoing radiotherapy in China.

- **Intervention Measures for the SHINE-MDT Group**

In the experimental group, patients would be treated with SHINE-MDT in addition to standard anti-oncologic treatment. The SHINE-MDT model with a fixed-site and fixed-membership organizational framework. The team consisted of specialists from radiation oncology, medical oncology, psychology, nutrition, rehabilitation, and nursing, with each discipline maintaining  $\geq 3$  core members. At least one representative from each key department attended every meeting. This team provided direct and prompt nutritional, psychological, and rehabilitation interventions tailored to the patient's needs. All departments participated consistently, facilitating mutual learning and collaborative decision-making.

- **Questionnaires Assessments**

Assessments were conducted through a series of questionnaire surveys, which included the European Organization for Research and Treatment of Cancer (EORTC) Quality-of-life Questionnaire Core 30 (EORTC QLQ-C30) and Head and Neck Cancer Module (EORTC QLQ-H&N35), NRS 2002, PG-SGA, DT, PHQ-9, and HADS. The PHQ-9 and HADS were evaluated every two weeks from radiotherapy initiation through the first-month post-treatment, while the other questionnaires were assessed weekly.

- **Frequency of Questionnaire Assessment**

Assessments were conducted at baseline (pre-radiotherapy) and weekly from radiotherapy initiation through the first-month post-treatment, followed by evaluations at 2, 3, and 6 months post-treatment.

**The end of radiotherapy:** The completion of radiotherapy is the final radiotherapy day, with administration permitted within a  $\pm 1$ -day.

**The middle of radiotherapy:** The middle of radiotherapy refers to the treatment period scheduled around half of the radiotherapy schedule, within  $\pm 1$  day. Additionally, if a

patient experiences an interruption in treatment before the scheduled middle evaluation, the timing of this intermediate assessment will be delayed accordingly.

**The post-treatment surveillance:** Post-radiotherapy follow-up visits at 1, 2, 3, and 6 months after treatment completion refer to assessments conducted within a window of  $\pm$  3 days relative to the specified monthly intervals.

eTable 1: Frequency of Questionnaire Assessments

| Test Item                                               | Testing Time Points                                                                                                                                                                     |
|---------------------------------------------------------|-----------------------------------------------------------------------------------------------------------------------------------------------------------------------------------------|
| Compliance with Radiotherapy                            | At the end of radiotherapy                                                                                                                                                              |
| EORTC QLQ-C30 Core Quality of Life Questionnaire        | Baseline (pre-radiotherapy) and weekly from radiotherapy initiation through the first-month post-treatment, followed by evaluations at 2, 3, and 6 months post-treatment.               |
| EORTC QLQ-H&N35 Head and Neck Cancer Specific Module    | Baseline (pre-radiotherapy) and weekly from radiotherapy initiation through the first-month post-treatment, followed by evaluations at 2, 3, and 6 months post-treatment.               |
| Nutritional Risk Screening Tool (NRS-2002)              | Baseline (pre-radiotherapy) and weekly from radiotherapy initiation through the first-month post-treatment, followed by evaluations at 2, 3, and 6 months post-treatment.               |
| Patient-Generated Subjective Global Assessment (PG-SGA) | Baseline (pre-radiotherapy) and weekly from radiotherapy initiation through the first-month post-treatment, followed by evaluations at 2, 3, and 6 months post-treatment.               |
| Distress Thermometer (DT)                               | Baseline (pre-radiotherapy) and weekly from radiotherapy initiation through the first-month post-treatment, followed by evaluations at 2, 3, and 6 months post-treatment.               |
| Patient Health Questionnaire-9 (PHQ-9)                  | Baseline (pre-radiotherapy) and once every two weeks from radiotherapy initiation through the first-month post-treatment, followed by evaluations at 2, 3, and 6 months post-treatment. |
| Hospital Anxiety and Depression Scale (HADS)            | Baseline (pre-radiotherapy) and once every two weeks from radiotherapy initiation through the first-month post-treatment, followed by evaluations at 2, 3, and 6 months post-treatment. |

- Quality control of questionnaire evaluations

To standardize questionnaire evaluations, we utilized video tutorials to assist patients in better understanding the self-rating questionnaires (EORTC QLQ-C30, EORTC QLQ-

H&N35, PG-SGA, DT, PHQ-9, HADS), enabling more accurate survey completion. For examiner-rated questionnaires (NRS 2002), nurses underwent collective training on the questionnaire content. They then conducted evaluations using standard patients to identify scoring discrepancies among different questionnaire-assessed nurses. This process enhanced understanding of the questionnaire content and reduced errors in examiner ratings.

For nutritional interventions, patients with an NRS 2002 score below 3 and a PG-SGA score below 4 were classified as having no or mild malnutrition. These patients received dietary guidance while continuing scheduled radiotherapy. For patients with a PG-SGA score of 4 or higher, different approaches were taken: those in the control group were referred to the nutrition department for consultation. In contrast, patients in the experimental group were coordinated by the risk-stratified nurses to receive individualized treatment from SHINE-MDT.

For psychological interventions, patients with mild or no psychological disorders (DT score < 4, PHQ-9 score < 10, and both HADS-A and HADS-D scores < 8) continued scheduled radiotherapy. When a patient met any of the following criteria: 1) the DT score  $\geq 4$ , 2) the PHQ-9 score  $\geq 10$ , 3) the HADS-A or HADS-D score  $\geq 8$ , the risk-stratified nurses recommended that patients in the UC group go to the mental health center for psychological counseling, while the risk-stratified nurses coordinated patients in the SHINE-MDT group to receive appropriate treatment from SHINE-MDT. Patients in the control group maintained in their assigned group throughout the study.

- Research Intervention Procedure

[figure not shown]

eFigure1: Research Intervention Procedure

abbreviation: SHINE-MDT: Supportive Holistic Interventions by Nurses and Experts via Multidisciplinary Team

- Nutritional and Psychological Intervention Process for the Usual Care Group

[figure not shown]

eFigure 2: Nutritional Intervention Process for the Usual Care Group

abbreviation: ONS: Oral Nutritional Supplements; PPN: Partial Parenteral Nutrition

[figure not shown]

eFigure 3: Psychological Intervention Process for the Usual Care Group; HADS-A: HADS-Anxiety; HADS-D: HADS-Depression

- Nutritional and Psychological Intervention Process for the SHINE-MDT

[figure not shown]

eFigure 4: Nutritional Intervention Process for the SHINE-MDT Group

abbreviation: SHINE-MDT: Supportive Holistic Interventions by Nurses and Experts via Multidisciplinary Team; ONS

: Oral Nutritional Supplements; PPN: Partial Parenteral Nutrition

[figure not shown]

eFigure5: Psychological Intervention Process for the SHINE-MDT Group

abbreviation: SHINE-MDT: Supportive Holistic Interventions by Nurses and Experts via Multidisciplinary Team;

HADS-A: HADS-Anxiety; HADS-D: HADS-Depressions

- Rehabilitation Intervention Process for the SHINE-MDT

Rehabilitation Physician: participates in MDT discussions, leads the patient's functional assessment, and formulates the rehabilitation prescription.

Specialized rehabilitation therapists then implement interventions if needed:

Speech Pathologist (SP): Addresses dysarthria, dysphonia, and dysphagia through articulation training, voice function rehabilitation, and swallowing therapy.

Occupational Therapist (OT): Manages orofacial dysfunction, ADL limitations, and cognitive deficits using adaptive equipment training, orofacial muscle strengthening, and cognitive strategy interventions.

Physical Therapist (PT): Treats motor dysfunction, pain, and lymphedema with therapeutic exercise and symptom management techniques.

Rehabilitation intervention reference for *American Cancer Society Head and Neck Cancer Survivorship Care Guideline*.

### 3.3 Contamination Control

- Spatial Segregation

The UC cohort received standard therapy (including radiotherapy) in the First Inpatient Department, while the SHINE-MDT cohort underwent identical protocols within a physically separated Medical Technology Building.

- Temporal Isolation

Treatment sessions for the MDT cohort were scheduled exclusively in morning blocks (08:00–13:00), with UC cohort sessions allocated to afternoon blocks (14:00–18:00). This eliminated unstructured patient interactions in shared waiting areas.

- Care Team Separation

MDT specialists (nutritional, psychological, and rehabilitation) were exclusively assigned to the intervention cohort and were not involved in UC cohort management.

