## 4. Study assessment

### 4.1 Rate of radiotherapy interruption assessment

The primary endpoint was the radiotherapy interruption rate. Radiotherapy interruption was defined as actual radiotherapy days minus planned radiotherapy days greater than or equal to 5 days, regardless of the causes for interruption. The radiotherapy interruption rate was calculated as the proportion of individuals in each group who experienced such a delay. Weekends and statutory holidays were counted into the planned radiotherapy schedule.

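### Radiotherapy building and time of day are fixed by arm, so facility or scheduling delay cannot be separated from the SHINE-MDT effect on an all-cause interruption endpoint

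*Protocol*

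**What the plan says.** Protocol section 3.3 sets out three kinds of separation between the arms. The first is by place: "The UC cohort received standard therapy (including radiotherapy) in the First Inpatient Department, while the SHINE-MDT cohort underwent identical protocols within a physically separated" building (the Medical Technology Building). The second is by time: "Treatment sessions for the MDT cohort were scheduled exclusively in morning blocks (08:00–13:00), with UC cohort sessions allocated to afternoon blocks (14:00–18:00"). The reason given for the time split is: "This eliminated unstructured patient interactions in shared waiting areas". The third is by staff: the MDT specialists work only with the intervention arm.

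Section 4.1 defines the primary event as "actual radiotherapy days minus planned radiotherapy days greater than or equal to 5 days, regardless of the causes for interruption". One allowance is made: "Weekends and statutory holidays were counted into the planned radiotherapy schedule". Machine downtime, servicing and lack of a treatment slot are not mentioned there or elsewhere in the protocol.

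Section 3.2 describes SHINE-MDT as nutritional, psychological and rehabilitation support from a fixed team. Neither the radiotherapy building nor the hour of treatment is part of it. Allocation is 1:1 in permuted blocks.

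**The concern.** Keeping the MDT staff and clinic away from usual-care patients is ordinary contamination control. Section 3.3 goes further and splits radiotherapy delivery by arm, and the primary endpoint is itself a measure of radiotherapy delivery. Randomisation balances the patients. It cannot balance conditions that are attached to the arm afterwards.

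If the two buildings or the two blocks differ in how often treatment days are lost and not made up, the difference enters the comparison of interruption rates directly. It could make an ineffective programme look effective, or hide an effective one. At stake is how much of an observed difference belongs to SHINE-MDT.

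**Working it through.** **1. The plan's own figure.** Section 6.1 gives 25% versus 10%, one-sided α 0.025, power 0.80, 5% dropout, 214 patients (107 per group). With pooled variance and no continuity correction:

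n = [1.960·√(2·0.175·0.825) + 0.842·√(0.25·0.75 + 0.10·0.90)]² / 0.15² = (1.053 + 0.443)² / 0.0225 ≈ 99.5, so 100 per arm.

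100/0.95 = 105.3, so 106 per arm and 212 in total. That is close to 214, so the sample size is not in question. Evaluable patients per arm: 107 × 0.95 = 101.65, taken as 101.

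**2. What can be estimated.** Write the log-odds of interruption as a + b₁·arm + b₂·building + b₃·slot. Under section 3.3 the three indicators take the same value in every patient, so only the sum b₁ + b₂ + b₃ can be estimated. Adding building or slot as a covariate does not help, and neither does a larger sample.

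The protocol names no machines, so there are two possibilities. If each building has its own equipment, building and slot are both tied to arm. If equipment is shared, slot still is.

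**3. How a facility delay becomes an event.** The threshold is 5 excess days and causes are pooled. A short outage alone does not reach it, but it adds to other lost days. As an illustration, 3 days lost to illness plus 2 lost to servicing make 5 and count as an interruption.

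**4. Size, over an assumed range.** The documents give no figure for a facility or slot effect. Let d be the assumed difference in interruption rate between the arms from that source alone. With x₁ interruptions in usual care and x₂ in SHINE-MDT, n = 101 per arm and p̄ = (x₁ + x₂)/(2n), the statistic is

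Z = [(x₁ − x₂)/n] / √(2p̄(1 − p̄)/n).

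The chance of declaring superiority is the sum of the binomial probabilities of all pairs (x₁, x₂) with Z > 1.960. The pooled z-test is itself an assumption, as section 6 names no test.

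| d (points) | No true effect, d favours SHINE-MDT: 25% vs 25% − d | No true effect, low base rate: 10% + d vs 10% | True 25% vs 10%, d against SHINE-MDT: 25% vs 10% + d |
|---|---|---|---|
| 0 | 2.5% | 2.6% | 82.0% |
| 2 | 5.2% | 6.7% | 67.8% |
| 3 | 7.2% | 9.9% | 59.8% |
| 5 | 13.4% | 18.9% | 43.5% |
| 10 | 43.5% | 52.2% | 13.4% |

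Usual care is given first in each pair. The first two result columns are false-positive risks and the last is power. With all 107 per arm and no true effect at 25%, d of 3, 5 and 10 points gives 7.5%, 14.0% and 45.2%. The extra patients do not reduce the bias.

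**5. Consistency of section 3.3.** It places the arms in physically separate buildings and then justifies the time split by waiting areas that are shared. If the buildings are separate for radiotherapy, the time split adds little protection. If areas or equipment are shared, the description of the spatial split is incomplete. The two statements need reconciling.

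**The case against.** The strongest reply is that the size is entirely assumed. Section 1 attributes interruptions mainly to nutritional and psychological causes. Against a 25% control rate, a 10-point facility difference would make 10/25 = 40% of usual-care interruptions a matter of building or slot. The 5-day threshold also screens out isolated outages. This stands: the 10-point row is an extreme, and the lower rows are the more realistic part of the range.

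Section 3.3 also says that the arms underwent the same protocols. That is fair for the regimen, but it does not say that capacity, downtime or make-up rules were matched.

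A reader might go further than the documents allow in three ways:

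- **That facility delay falls all on usual care.** Downtime in either building falls on that building's own arm, and a net difference needs unequal rates, which nothing in the protocol shows. Nor can a morning overrun in one building push back the afternoon list in another.
- **That the 4-hour block leaves usual care short of slots compared with the 5-hour block.** This matters only if capacity binds. The protocol gives no machine count, session length or non-trial load, and 107 per arm is a cumulative total, not a daily one.
- **That mixing the arms would be harmless.** Contact would probably dilute the effect, but usual-care patients who see the extra support could be discouraged, so the direction is not certain.

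Finally, a sensitivity analysis by cause is ordinary SAP content, and the SAP is not at hand. Its absence from the protocol is therefore not the fault. The fault is the design in section 3.3 combined with the endpoint in section 4.1.

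**Conclusion.** The concern holds as a problem of identification, not as a demonstrated bias. Arm, building and slot coincide by design, the endpoint counts every cause, and covariate adjustment cannot separate them. A facility difference of 5 points, one third of the planned 15-point effect, would raise the one-sided false-positive risk from 2.5% to about 13%, or lower power from 82% to about 43% if it ran the other way. These figures rest on an assumed difference, 101 evaluable patients per arm and a pooled z-test. Separate machines are inferred from separate buildings.

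It would be tempting to conclude that a positive result could not be attributed to SHINE-MDT at all. The documents do not support that. The size of any facility effect may be small, and causes of delay taken from treatment records can remove much of this pathway even though regression adjustment cannot. What follows is that attribution has to be shown and cannot be taken from randomisation alone.

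**What to change.** **Patients still to be treated.** Drop the arm-specific time blocks, and confine segregation to the MDT clinic and staff where possible. The cost is a scheduling change and some contact between arms. Putting both arms on the same machines is a larger trade-off against contamination. Section 3.3 is in the past tense, so either change may come too late.

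**All patients.** Take building, machine, slot and cause of each missed day from the radiotherapy record. The case report form in Appendix 5, as shown, has no field for these. Have causes classified without knowledge of arm where possible. Because building and slot reveal the arm, they should be hidden from whoever classifies the cause.

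**Analysis.** Before results are seen by arm, pre-specify a sensitivity analysis of the primary endpoint that does not count days lost to machine, maintenance or scheduling causes, unless the SAP already has one. The cost is record retrieval and one further analysis.

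**Reporting.** State the machines, capacity, downtime and make-up rules for each building and block, and reconcile the shared waiting areas with the separate buildings. Unless the sensitivity analysis agrees with the primary result, limit the conclusion to the package of SHINE-MDT plus its building and slot.
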